## Abstract

**Background::**

Vascular dementia (VaD) is the 2nd most common subtype of dementia after Alzheimer disease. Currently, there are no medications approved for treating patients with VaD. Tianmabianchunzhigan (TMBCZG) tablet is an active ingredient extracted from *Gastrodia* that has been reported to improve memory and other cognition. And the TBMCZG has been approved clinical trial with patients with VaD by center for drug evaluation of China (CFDA). To evaluate the efficacy, safety, and tolerability of TMBCZG tablets in the treatment of mild to moderate VaD, we designed and reported the methodology for a 24-week, randomized, double-blind, parallel, placebo-controlled, multicenter trial.

**Methods::**

A total of 160 patients with mild to moderate VaD will be enrolled. After a 2-week run-in period, the eligible patients will be randomized to receive either TMBCZG high-dose group (TBMCZG 3 tablets, twice per day); TMBCZG middle-dose group (TMBCZG 2 tablets and placebo 1 tablet twice per day); TMBCZG low-dose group (TMBCZG 1 tablet and placebo 2 tablets, twice per day); placebo group (placebo 3 tablets, twice per day) for 24 weeks, with a follow-up 12 weeks after withdrawn drug treatment. The primary efficacy measurement will be the vascular dementia assessment scale-cognitive subscale and the Clinical Dementia Rating-Sum of the Boxes scale. The secondary efficacy measurements will include the mini mental state examination and activities of daily living. Adverse events will also be reported.

**Discussion::**

This randomized trial will be the 1st rigorous study on the efficacy and safety of TMBCZG tablets for treating cognitive symptoms in patients with VaD using a rational design.

**Trial registration::**

ClinicalTrials.gov NCT03230071. Registered on July 26, 2017.

## Introduction

1

Vascular dementia (VaD) is a very frequent form of dementia, it had reported that dementia develops in around 15% to 30% of subjects 3 months after a stroke.^[1]^ At present, the treatment of VaD focuses on primary and secondary prevention strategies because randomized clinical trials in VaD have not been able to demonstrate clinically relevant symptomatic improvement. Although most have shown a small but significant benefit of cholinesterase inhibitors on cognition, the magnitude of this effect has been slight and benefits on global functioning, activities of daily living (ADL), and behavior have not been consistently reported; thus, cholinesterase inhibitors or memantine were not authorized for patients with VaD.^[2]^ Additionally, it has not yet been possible to establish disease-modifying effects in VaD syndrome.^[3]^ Thus, the development of an effective therapy for VaD is important.

Tianmabianchunzhigan tablet (TMBCZG) is an active ingredient extracted from *Gastrodia* (Tianma in Chinese) by Peking Union Second Pharmaceutical Factory. Preclinical studies have shown that TMBCZG can improve the learning and memory ability of rats with VaD and reduce the neuropathologic damage of model rats. A human tolerability test in a healthy person showed that the maximum tolerated dose of the drug was 84 mg/d, and the excessive adverse reactions were elevated urinary *N*-acetyl-β-d-glucosaminidase enzyme, hypotension, and diarrhea. In addition, toothache, sinus tachycardia, and elevated microalbuminuria for other suspected adverse events are further recommended for observation in expanded population samples. And the TBMCZG has been approved clinical trial with patients with VaD by center for drug evaluation of China (CFDA). To further investigate the safety, efficacy and effective dose of TMBCZG tablets in the treatment of mild to moderate VaD, we designed and report the methodology for a 24-week randomized, double-blind, parallel, multicenter study.

## Methods

2

### Study design, ethic, and setting

2.1

This ongoing study is designed as a randomized, double-blind, parallel, placebo-controlled, multi-central trial. It involves a single-blind run-in period using placebo only (2 weeks) and a double-blind treatment phase after randomization (24 weeks). It has been approved by the China Food and Drug Administration (code: 2012L02385). Ethics approval was requested and approved through the Institutional Review Board of Dongzhimen Hospital, Beijing University of Chinese Medicine (DZMEC-JG-2016-108) and has been registered with ClinicalTrials.gov (ClinicalTrials.gov NCT03230071) on July 26, 2017. The present study protocol (version 3, May 19, 2017) is designed in accordance with the Good Clinical Practice Guidelines and the principles of the Declaration of Helsinki. The protocol design is based on the guidelines of standard protocol items: recommendations for interventional trials (SPIRIT), and the study results will also be reported according to these guidelines. The patients and responsible caregivers will provide written informed consent. The study will be carried out at Dongzhimen Hospital and some other centers in China. A schematic of the trial protocol is detailed in Figure 1.

**Figure 1 F1:**
[figure not shown]
Study flow chart.

### Participants

2.2

This trial will enroll both Chinese-speaking males and females, participants’ inclusion criteria are described as follows: Patients meeting the clinical diagnosis of probable VaD established according to the National Institute of Neurological Disorders and Stroke and the Association Internationale pour la Recherche et l’Enseignement en Neurosciences (NINDS-AIREN)were eligible to participate^[4]^: dementia defined by clinical core criteria; cerebrovascular disease, defined by history of stroke and through a magnetic resonance imaging (MRI) scan, including infarct in the main blood vessels, single strategic infarct (e.g., thalamus, angular gyrus, and basal forebrain), multiple lacunar infarcts, and/or extensive white matter damage surrounding ventricles (≥25% of all white matter area), hemorrhage^[5]^; a relationship between dementia and cerebrovascular disease, manifested, or inferred by the presence of one or more of the following: onset of dementia within 3 months following a recognized stroke; abrupt deterioration in cognitive functions; or fluctuating, stepwise progression of cognitive deficits.

Other inclusion criteria including:

1.mild to moderate dementia, defined with mini mental state examination (MMSE) score of ≤26 and ≥11^[6]^;2.aged ≥55 and ≤80 years old; weighing of ≥45 and ≤90 kg;3.adequate vision and hearing ability to complete all study tests;4.have a stable caregiver;5.can read simple articles and write simple sentences;6.informed consent, signed informed consent by legal guardian.

They will also be assessed for the following exclusion criteria:

1.A medical history of other dementia types, like Alzheimer disease, frontotemporal dementia, Parkinson disease dementia, dementia with Lewy bodies, Huntington disease, etc;2.Subdural hematoma, traffic hydrocephalus, brain tumor, thyroid disease, vitamin deficiency, or other diseases which can lead to cognitive impediment;3.Major depression (Hamilton depression rating scale [HAMD] ≥17)^[7]^ or major anxious (Hamilton anxiety rating scale [HAMA] ≥12)^[8]^;4.Subject cannot complete related test due to severe neurologic deficits, such as hemiplegia, aphasia, audio-visual disorder, and so forth;5.Severe cardiovascular disease (severe arrhythmia, myocardial infarction within 3 months, New York Heart Association Functional Classification III and IV, systolic pressure ≥180 or ≤90 mm Hg);6.Severe liver or kidney dysfunction (alanine aminotransferase or aspartate transaminase is more than 1.5 times the upper limit of normal, or serum creatinine is more than the upper limit of normal);7.Uncontrolled diabetes (glycosylated hemoglobin is more than 2 times the upper limit of normal);8.Asthma, chronic obstructive pulmonary disease, multiple neuritis, myasthenia gravis, and muscle atrophy;9.Severe indigestion, gastrointestinal obstruction, gastric and duodenal ulcers, and other gastrointestinal disorders that can affect drug absorption;10.A medical history of epileptic history, glaucoma, alcoholism, or psycho-substance abuse;11.Subject has been taking cholinesterase inhibitors, memantine, nimodipine, or herbal medicine which have function to improve cognition in the past 1 month;12.Use of sympathomimetic or antihistamines drugs within 48 hours before assessment;13.Allergic constitution or allergic reactions to experimental drug;14.According to the assessment of the investigator, subject cannot complete the study due to poor compliance or other reasons;15.Subject is participating in other clinical trials or participated in the past 1 month.

### Intervention

2.3

The TMBCZG tablet will be supplied by the Peking Union Second Pharmaceutical Factory. Each tablet weighs 0.1 g, which contains *Gastrodia* organic benzyl polyglycolate 14 mg. The TMBCZG tablets were produced in a single batch (batch number: 161101-kb, placebo batch number: 170201-kb) in strict compliance with standards of good manufacturing practice. During the 2-week placebo washout period, all patients will receive 3 placebo tablets twice times per day. During the double-blind, the patient will be randomized to TMBCZG high-dose group (TBMCZG 3 tablets, twice per day); TMBCZG middle dose group (TMBCZG 2 tablets and placebo 1 tablet twice per day; TMBCZG low-dose group (TMBCZG 1 tablet and placebo 2 tablets, twice per day); placebo group (placebo 3 tablets, twice per day). To preserve blinding, the placebo tablets have an identical taste and appearance to the TMBCZG tablets.

Concomitant use of anticonvulsants, antipsychotics, cholinomimetic drugs, anticholinergic agents, anti-Parkinson drugs, cholinesterase inhibitors, memantine, nootropic drugs, nimodipine, other cognition enhancers, traditional Chinese medicine tonic, or any drugs containing *Gastrodia* will be forbidden. The investigator must record the concomitant drugs, including the name of the drug, daily dose, reason for using, and date of termination.

### Efficacy measurements

2.4

The primary efficacy measurements are changes of the vascular dementia assessment scale-cognitive subscale (VADAS-cog/17 items)^[9]^ and the clinical dementia rating-sum of the boxes (CDR-SB)^[10]^ scale from baseline to the 24th week after treatment. VADAS-cog is a revision of the ADAS-cog to be a better measure in vascular conditions,^[11]^ and a higher score indicates higher impairment. In addition to ADAS-cog, the VADAS-cog comprises additional frontal lobe tests reflecting attention, working memory, executive function, and verbal fluency.^[9]^ It was suggested that the VADAS-cog may be a more sensitive endpoint in patients with white matter load and vascular burden of the brain than ADAS-cog.^[12]^

The CDR-SB is a standard for disease grading in clinical studies of dementia and is used for overall endpoint assessment in clinical trials. It comprehensively assesses the cognitive and functional aspects of dementia patients, including memory, orientation, judgment and problem-solving skills, social affairs, family and hobbies, and personal cooking. The CDR-SB scores from 0 to 18 points, and a higher score indicates higher impairment.

The secondary efficacy measurements include the MMSE and ADL scale.^[6,13]^ The MMSE is used to assess the global cognition. ADL was used to measure the physical self-maintenance ability and instrumental ADL ability.^[13,14]^

### Safety assessment

2.5

The safety assessment will include the following: vital signs: physical examination of vital signs, including rate of breathing, heart rate, and blood pressure; electrocardiography; the laboratory parameters included complete blood count, urine routine test, fecal routine and occult blood test, hepatic and renal function, coagulation function and electrocardiogram (ECG); and any adverse events that may occur, including the types of adverse events, time of occurrence, duration, treatment measures, and evaluation of the correlation between the tested drugs and the adverse event (positive, probable, possible, or not correlated); the severity of the adverse event (mild, moderate, and severe) must be evaluated.

### Evaluation time point

2.6

The efficacy measurement will be assessed at baseline (week 0), at the midpoint (week 4 and week 12), and at the endpoint (week 24), 12 weeks after withdrawal (week 36).

The safety assessments will be evaluated at the baseline (week 0), at the midpoint (week 4, week 8, and week 12), and at the endpoint (week 24).

### Sample size

2.7

There are no similar studies using TMBCZG tablets to treatment patients with VaD for the proposed study duration (24 weeks). The sample size was calculated based on the primary endpoints, VADAS-cog. It is hypothesized that the efficacy of TMBCZG in the treatment of mild to moderate VaD is similar to that of donepezil. Previous studies reported that the mean changes of ADAS-cog scores after 5 and 10 mg donepezil treatment were (5.75 ± 7.44) points and (2.25 ± 7.44) points, respectively. We assume that the placebo control group has a certain progression after 24 weeks’ treatment (△ = −0.25). The mean scores of the 3 groups of VADAS-cog scale improvement were set at equal intervals, that is, the changes before and after the scores of each group were −0.25, 0.75, 1.50, 2.25, and the variance of the 4 groups of VADAS-cog means 1.14. The standard deviation within is 7.44 points. For this phase IIa study, the 2-sided test level α = 0.20 and the power 1-β = 0.50. This clinical trial adopts a balanced design and uses nQuery Advisor 7.0 to calculate, 32 cases are needed for each group. Considering a greater rate of discontinuation of 20%, the sample size was increased to 39 per group to ensure adequate patients to complete the study. The total number of cases was 160 cases, that is, 40 cases in the placebo control group and 40 cases in the 3 dose groups of the TMBCZG tablets. Note also that because this study is a pilot efficacy study (phase IIa), a larger sample size to reach a higher degree of statistical power is not required.

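### The variance of the group means (1.14) uses divisor 3 where the power formula needs 4, so 32 per group gives 44% power, not 50%; 50% needs 42

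*Protocol article*

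**What the plan says.** Everything is in section 2.7 (Sample size) of the protocol article. The calculation is based on VADAS-cog.

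- Assumed improvements, placebo first: "the changes before and after the scores of each group were −0.25, 0.75, 1.50, 2.25".
- Spread of those means: "the variance of the 4 groups of VADAS-cog means 1.14".
- Within-group variability: "The standard deviation within is 7.44 points".
- Error rates: "the 2-sided test level α = 0.20 and the power 1-β = 0.50".
- Result: "This clinical trial adopts a balanced design and uses nQuery Advisor 7.0 to calculate, 32 cases are needed for each group".
- Allowance for dropout: "Considering a greater rate of discontinuation of 20%, the sample size was increased to 39 per group".
- Enrolment: "The total number of cases was 160 cases", which is 40 per group.

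The section does not name the test. A variance of four group means is an input to the overall F test of a one-way ANOVA, and that test reproduces the stated 32.

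**The concern.** A variance of group means can be computed with divisor G − 1 (a sample variance) or divisor G. As a description of four numbers, either is acceptable. In an ANOVA power calculation the choice is fixed, because the noncentrality depends on the sum of squared deviations itself. If the formula multiplies the variance by G = 4, the variance must have been formed with divisor 4. The stated 1.14 looks like the divisor-3 version. That would make the assumed differences between groups appear larger than the listed means imply, and the sample size too small for the claimed power.

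This is the only power statement in the article. A reader interpreting a null result, or planning the next trial from this one, will take from it that the design had an even chance of detecting the assumed dose response.

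**Working it through.** **Inputs** (all from section 2.7): means −0.25, 0.75, 1.50, 2.25; SD 7.44, so SD² = 55.3536; alpha 0.20; target power 0.50; G = 4 equal groups.

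**Step 1: spread of the means.**
- Grand mean = (−0.25 + 0.75 + 1.50 + 2.25)/4 = 1.0625.
- Deviations: −1.3125, −0.3125, 0.4375, 1.1875.
- Squares: 1.7227 + 0.0977 + 0.1914 + 1.4102 = 3.4219 (unrounded 3.421875).
- Divided by 3: 1.1406, the stated 1.14.
- Divided by 4: 0.8555.

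**Step 2: formula.** For n per group, power = P(F′ > F(1 − alpha; 3, 4(n − 1))), where F′ is noncentral F with noncentrality

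λ = n × (sum of squared deviations)/SD² = n × 4 × V/SD².

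The two forms agree only if 4V = 3.4219, that is, V = 0.8555.

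**Step 3: reproduce the protocol's figure with V = 1.14.**
- n = 31: λ = 31 × 4.56/55.3536 = 2.554, power 0.498.
- n = 32: λ = 32 × 4.56/55.3536 = 2.636, power 0.506.

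The smallest n reaching 50% is 32, exactly as stated. The calculation therefore used 4 × 1.14 = 4.56 where the means give 3.42, a ratio of 4/3.

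**Step 4: correct noncentrality, everything else unchanged.**

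| n per group | λ = n × 3.421875/55.3536 | Power at alpha 0.20 |
|---|---|---|
| 32 | 1.978 | 0.437 |
| 40 | 2.473 | 0.491 |
| 41 | 2.535 | 0.497 |
| 42 | 2.596 | 0.503 |

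So 42 per group are needed. With 20% loss, 42/0.8 = 52.5, rounded up to 53 per group, or 212 in total. A simulation from the four means agrees: 0.439 at 32 and 0.505 at 42.

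**Step 5: could another route have given 32?**
- High dose against placebo alone (difference 2.50) needs 30 per group by the normal approximation, or 29 by the exact t test.
- A linear trend contrast already has about 51% power at 28.
- Exactly equal spacing of all four means gives 41 with divisor 4 and 31 with divisor 3.

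None of these gives 32, and the first two would not use a variance of four means.

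**Side check on the SD.** Section 2.7 takes 7.44 from ADAS-cog results, while section 2.4 says VADAS-cog adds further tests to ADAS-cog. If the VADAS-cog SD were 9 or 10 (an assumption; the document gives no value), power with 32 per group would be 0.37 or 0.34. The divisor error does not depend on this.

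**The case against.** The strongest reply is that this changes little. The protocol describes a phase IIa pilot, sets alpha at 0.20 and power at 0.50 deliberately, and says more power is not needed; no decision rule turns on 50% rather than 44%. That stands as a reason to keep the sample size. It justifies aiming for 50%, but not reporting 50% when the inputs give 44%.

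Second, 32 per group is the pessimistic end. Section 2.12 analyses everyone with one dose and one on-treatment primary evaluation, carrying the last observation forward, so some dropouts remain in the analysis. This is fair: the relevant n lies between 32 and 40, and power between 0.437 and 0.491. The top of that range is less than one point below 50%, but still below it.

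Third, section 2.12 plans an ANCOVA adjusted for baseline and center, which may be more efficient than the unadjusted F test. If baseline correlated 0.3 with change (assumption), multiplying the SD by √(1 − 0.3²) gives 0.458 at 32 and 0.515 at 40; a correlation of 0.5 gives 0.506 at 32. Such a gain could offset the error, but section 2.7 neither claims it nor states a correlation.

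Fourth, section 2.12 declares significance at 0.05, not 0.20. At 0.05 the same means give 0.186 with 32 and 0.226 with 40. This loss is larger than the divisor's, but it is a separate matter. It is why any restated power must carry its alpha.

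Finally, it would be loose to say that the effect is overstated by one third. The variance of the means and the noncentrality are. The standardised effect, √V/SD, rises from 0.124 to 0.144, about 15%.

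**Conclusion.** The concern holds. The 1.14 is a divisor-3 variance used where divisor 4 is required, and this use reproduces the stated 32 per group. On the protocol's own means, SD and alpha of 0.20, power is 0.437 with 32 per group, about 6 points below the stated 0.50. It is 0.491 if all 160 patients are analysed. Reaching 50% takes 42 per group rather than 32.

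These figures assume an unadjusted overall F test with equal groups. That test is inferred from the inputs and confirmed by the match at 32. The result does not depend on any software convention, because the noncentrality is fixed by the listed means. The practical consequence is an incorrect power statement in a trial that accepts low power by design; it does not by itself call for more patients.

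**What to change.** In section 2.7, replace 1.14 with 0.855 and state that it is the sum of squared deviations divided by the number of groups. Name the overall F test. Keep 160 patients and give its power as about 0.44 with 32 completers per group and 0.49 with 40, labelled as at alpha 0.20. Report that 50% would take 42 evaluable per group.

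Two additions are useful but not needed for the correction:

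- Show power over a range of SDs, because 7.44 is an ADAS-cog figure.
- If the sponsor wants to meet the 50% target with the present numbers, prespecify a linear dose-trend contrast as the primary test before unblinding. With weights −3, −1, 1, 3 the contrast of the assumed means is 8.25 and its standard error is 7.44 × √(20/32) = 5.88. The ratio is 1.40 and the power about 0.55 with 32 per group at two-sided alpha 0.20. This is a change of design, to be chosen on its merits.

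The correction itself costs one rewritten paragraph and a slightly less favourable power figure, with no more patients.

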### Procedures

2.8

Two methods are being used to recruit participants with VaD. The 1st source of subjects is from memory clinics of different research centers, and the 2nd source is those who respond to advertisements published in local newspapers. Advertisements will be placed in local papers in surrounding the research centers; internet advertisements will be several website placed on different research centers.

Participants will undergo an initial face-to-face interview after written informed consent is obtained from both the participant and her informant, the participant's medical history and demographics will be taken with a semi-structured clinical interview, and participants will be estimated cognitive function using MMSE, HAMD, HAMA. Researchers will assess them against the study's inclusion and exclusion criteria, and the appropriate subjects will be initially selected. The subjects who decided to enroll will be assigned to run-in period. After 2 weeks run-in period, the subjects will be evaluated MMSE, VADAS-Cog, CDR-SB, ADL and vital signs, 12-lead ECG, laboratory tests, skulls MRI. Inclusion and exclusion criteria will be assessed again. And then subjects will be randomized to different treatment groups. Schedule of interventions and assessments at screening baseline, midpoint, and endpoint sessions is shown in Table 1.

**Table 1 T1:**
[figure not shown]
Schedule of interventions and assessments at screening baseline, midpoint, and endpoint sessions.

After baseline measurements, the first 4 weeks of medication will be dispensed. And the medication will be dispensed every 4 weeks. Participants will be required to return any unused medication at midpoint and endpoint; this will be used to determine compliance.

### Study drug termination criteria

2.9

1)Prior to the maximum treatment period of 24 weeks, study drug will be discontinued if any of the following conditions are met:2)Patient or informant request termination of study drug;3)Patient or informant withdraws consent for the study;4)Noncompliance with study drug as determined by the investigator (patients who have taken 80% or more of the expected number of tablets will be considered compliant);5)Decision by the investigator that the study drug should be discontinued on safety grounds;6)The reason for study drug termination should be recorded and any unused medication returned to pharmacy.

After the protocol is approved by the Ethics Committee, if modified, it must be reported to the Ethics Committee before execution and also recorded in the drug administration department.

